**Outcome and process indicators**

The primary maternal outcome measure is the completion rate of essential maternal care. We define a continuum of care completion as follows:

1. fully completed care when a mother has received four or more antenatal care, delivered in a health facility with a skilled attendant, and received at least four postnatal care (first 24 hours, 48-72 hours, 7-14 days, and six weeks after delivery) from HEWs or other health professionals within the first month after delivery. Because maternal completion of these essential care components will have an implication for newborn health and survival, and essential newborn care is given simultaneously during delivery and postnatal care, the completion of essential newborn care will be analyzed in relation to the maternal completion rate.
2. Emergency home-based care when the delivery occurred at home and mother and baby received immediate visit at home by HEWs or a higher health professional.
3. Sub-analysis on the primary outcome will compare intervention with control clusters separately on antenatal care completion rate, rate of facility delivery, proportion of assistance received immediately form HEWs or other professionals when a birth occurred at home, and proportion of mothers who stayed at maternal waiting shelters immediate days before delivery.
4. Proportion received financial, transport, and family care support from community resource persons (COLs) when a support is critically needed.
5. The proportion of newborn babies received the four essential newborn care services (immediate and thorough drying, skin-to-skin contact, immediate breastfeeding initiation, and delayed cord clamping)
6. Emergency newborn sickness identification and referral rates.
7. Secondary outcome measure will be on whether the intervention affected reduction of neonatal mortality and stillbirth rates.

For newborn babies, we will measure and compare with the control arm the proportion of babies immediately put to breastfeeding and exclusively feeding until at least a month after birth, the proportion of babies received essential thermal care (wrapping in close, skin-to-skin contact to mother immediately, delayed baby bathing), baby resuscitation at home and in clinics, and proportion of babies received emergency treatment and referrals when they had danger signs.

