# Summary

**Background:** **Background:** Maternal and newborn mortality and morbidity remain high in low- and middle-income countries such as Ethiopia. Limited access and dropouts from essential continuum of care interventions are critical factors. In Ethiopia about one in five complete the continuum of essential care through pregnancy, childbirth, and postnatal period Ethiopia. Evidence is limited on whether a package of interventions involving key community health actors increase the proportion completing essential maternal and newborn healthcare continuum in rural Sidama regional state, Ethiopia.

**Objective:** This study aims to implement and evaluate the effectiveness of community-based interventions designed to enhance involvement of key community health actors to improve completion rate of continuum of maternal care and utilization of newborn care.

**Methods:** Twenty rural kebeles (clusters) in Sidama Regional State, Ethiopia, are randomly allocated to intervention and control arms. A total of 2000 pregnant women, 1000 per arm, will be recruited between 20^th^ and 26^th^ week of gestation after intervention. Then they will be followed until six weeks postpartum between June 2024 and February 2025. In the intervention arm, mothers and newborns will receive targeted interventions at home and in their community through a package of interventions designed to improve completion rate of recommended maternal and newborn care. Control clusters will receive normal care from the state public health system. Primary outcomes will be the difference in the completion of continuum of maternal care and essential and emergency newborn care between intervention and control clusters measured by composite indicator constructed from variables. Secondary outcomes include rates of antenatal care completion, facility deliveries with skilled care, completion of at least four postnatal care, essential newborn care, and emergency identification and referrals, mortality measures.

**Conclusion:** This trial will implement and evaluate community-based intervention package within existing community healthcare infrastructure to produce evidence for informed policy and practice to achieve improved community-based healthcare.

**Budget:** A tentative budget plan will be **2,569,415**birrs, which will be secured from NORHED-II (SENUPH-II) project.

Key words: continuum of care, maternal, neonatal health care, community resource group.

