One such innovative approach is the Ethiopian Health Extension Program (HEP), a flagship national program rolled out in 2003 by Ministry of Health of Ethiopia (9). In each village of about 5,000 population, two women known as Health Extension Workers (HEWs) trained for one year in general health are placed in a satellite health post to provide health promotion and disease prevention services to residents. These women are permanent employee of Ethiopian government with monthly salary.

The Health Extension Program (HEP) has been instrumental in expanding access to primary healthcare services, demonstrating the feasibility and impact of deploying health extension workers (HEWs) in rural settings. From 2012, another voluntary network of about 30 women per village known as women development team (WDT) were introduced to support the works of HEWs, creating a strong network closer to households. Consequently, a systematic review by Yibeltal Assefa and colleagues showed that the HEP has significantly improved essential preventive and health promotion indicators HEP (10). Yet, concerning the skills of the HEWs to provide essential maternal and newborn care, a study identified up to 88% of HEWs had poor knowledge of neonatal danger signs and expressed that they are not confident enough to attend deliveries (11). This underscores the importance of an approach that improves their confidence, skills, and integration with health facilities.

Furthermore, a 2022 article by Tiruneh GT and colleagues demonstrated that overall, only one-fifth (20%) of women who initiated the first antenatal care completed the continuum of recommended essential care that combines completion of antenatal care, skilled birth attendance, and critical postpartum care (12).

One of the challenges in maternal and newborn care continuum in poorly organized health systems is low proportion of women having postnatal contact with competent health professionals. In 2022, WHO published guidelines for postnatal care and recommends at least four such contacts in the key time periods during the first 24 hours, 48-72 hours, one-two weeks and six weeks after birth (13). Without successful completion of postnatal care during these key periods, it is difficult to succeed in improving the continuum of care.

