**Objectives:**

1. To evaluate whether a set of community-based intervention improve completion of maternal continuum of care : A) The overall completion rate with composite result of combination of at least four antenatal care contacts, delivery in a health facility with skilled provider, and at least four postnatal care contacts and completion rates of each three components of the continuum of maternal care. B) Explore the experience of mothers and care providers on the effect of the intervention for maternal care, including the challenges and opportunities.
2. To determine the effectiveness of the community-based strategies on improving utilization of essential and emergency newborn care: A) WHO recommended four elements of essential newborn (immediate and thorough baby drying, skin-to-skin contact, initiation of early breast feeding within first hour, and delayed cord clamping). B) identification and referral of severely sick babies such as babies with danger signs. C) Cost-effectiveness of the intervention on improving maternal and newborn continuum of health care.

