The fourth round of data will be collected two weeks after delivery (10 days after the third data collection) on key first week survival, first week occurrence of morbidity, emergency help received for those who had serious sickness and utilization of postnatal care during the WHO recommended 7-14 days after birth, and essential baby care within the first two week. The final and fifth round of data collection will take place six weeks after delivery. This data collection will include variables on the first month and six week essential postnatal maternal and neonatal care, first month and six-week survival of the newborn, and information on sickness and emergency healthcare received for sickness in this period.

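### The primary outcome definition contradicts itself: it lists a six-week postnatal contact but confines the contacts to the first month

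*Protocol*

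**What the plan says.** In the Protocol, Outcome and process indicators, item 1 defines full completion as four or more antenatal contacts, facility delivery with a skilled attendant, and a postnatal component. For that component a mother must have "received at least four postnatal care (first 24 hours, 48-72 hours, 7-14 days, and six weeks after delivery". The sentence then continues with a second time limit: "six weeks after delivery) from HEWs or other health professionals within the first month after delivery".

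Other sections bear on the same component:

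- **Objectives, 1A** describes the composite as "at least four antenatal care contacts, delivery in a health facility with skilled provider, and at least four postnatal care contacts", with neither windows nor a one-month limit. The Summary also speaks only of at least four postnatal contacts.
- **Introduction** reports the guideline schedule as "at least four such contacts in the key time periods during the first 24 hours, 48-72 hours, one-two weeks and six weeks after birth", with no one-month limit.
- **Summary** sets the follow-up: "Then they will be followed until six weeks postpartum between June 2024 and February 2025".
- **Data collection** follows the windows. Round three (day four) covers the first two, round four (two weeks) covers the third, and for the last, "The final and fifth round of data collection will take place six weeks after delivery". That final round covers both first-month and six-week care.
- **Sampling strategy and sample size** takes completion of this continuum from 20% to 30% and arrives at 723 mother-baby pairs per arm. The plan is to recruit 1000 per arm.

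**The concern.** The two time limits sit in one sentence and cannot both hold. Anyone who programs the primary outcome has to drop something the definition says, and the protocol gives no rule for what to drop. The ways of doing so are different endpoints. They can give different completion rates and, because the intervention works partly through home postnatal visits by HEWs, different contrasts between arms.

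The stake is the credibility of the primary result. If the reading is chosen after data have been compared by arm, the trial cannot show that the choice was independent of the result. The sample size is also affected, because the 20% and 30% behind it are not tied to any one reading.

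**Working it through.** **1. The plan's own figure.** Inputs from Sampling strategy and sample size: control 0.20, intervention 0.30, z-values 1.96 and 0.84, m = 150, ICC = 0.01.

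- Before clustering: (1.96 + 0.84)² × (0.20 × 0.80 + 0.30 × 0.70) / 0.10² = 7.84 × 0.37 / 0.01 = 290.08 per arm.
- Standard design effect: 1 + (150 − 1) × 0.01 = 2.49.
- 290.08 × 2.49 = 722.3, rounded up to 723. The stated figure is reproduced. (The bracket as printed would give 1.5 and about 435, so 723 comes from the standard form. That is a side point.)

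The sample size therefore rests on the completion composite, and its inputs do not say how the postnatal component was defined.

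**2. The contradiction.** Six weeks = 42 days. One month = 28 to 31 days. Since 42 > 31, the fourth listed contact lies outside the stated limit. If all four windows are mandatory and the month is enforced, the set of completers is empty in both arms.

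**3. The readings that remain.** Each discards part of item 1.

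- A, four windows through six weeks: discards the one-month limit.
- B, three windows within a month: discards the six-week contact, and with it the count of four.
- C, any four contacts within a month: discards the listed timings, at least the last.

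Four constructed contact patterns, for women who meet the antenatal and delivery components:

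| Postnatal contacts | A | B | C | Literal |
|---|---|---|---|---|
| 12 h, 60 h, day 10, day 42 | yes | yes | no | no |
| 12 h, 60 h, day 10 | no | yes | no | no |
| 12 h, day 5, day 20, day 25 | no | no | yes | no |
| 12 h, 60 h, day 10, day 25 | no | yes | yes | no |

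Every woman who meets A meets B, so the rate under B is at least the rate under A. A and C are not nested, so the protocol does not say which of those two is higher.

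**4. What a different rate would do to power.** With 1000 per arm in 10 clusters, m = 100 and the design effect is 1 + 99 × 0.01 = 1.99, an effective 1000 / 1.99 ≈ 502.5 per arm. Two-sided 5% test of two proportions, large-sample approximation. Only the first row uses the protocol's rates; the others are assumptions that show the range.

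| Control vs intervention | Power |
|---|---|
| 20% vs 30% (planned) | about 96% |
| 30% vs 40% (assumed) | about 92% |
| 10% vs 15% (assumed) | about 67% |
| 5% vs 10% (assumed) | about 85% |
| 5% vs 7.5% (assumed) | about 37% |

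These rows do not predict the rate under any reading. They show that the protocol's margin depends on which endpoint the 20% and 30% describe.

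**The case against.** The best defence is that this is one stray phrase. Follow-up, the guideline schedule and the data rounds all run to six weeks, so the intended meaning is fairly clear. That stands as evidence for which way to correct the text. It does not remove the phrase from the operative definition, and no section says that the six-week limit prevails.

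Several stronger readings are tempting, and the documents do not support them:

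- **Completion will be 0% in both arms.** This follows only if every listed window is mandatory and the month is enforced. A looser reading can be met, at the price of ignoring part of the sentence.
- **The outcome is bound to be redefined after the fact.** Round five covers both first-month and six-week care, so the data will support a correction made beforehand. A statistical analysis plan, not shown here, may already choose a reading. Redefinition is a risk, not a certainty.
- **Objective 1A is a further conflicting definition.** A short objective expanded by a later definition is normal, and the two are compatible. It simply cannot settle the conflict.
- **A six-week contact made slightly late will be coded as absent.** No coding rule is given, and data also come from facility records. An interview at six weeks may miss a late contact. That is a secondary possibility.
- **The gap between readings can be sized by assuming a chance per window.** With independent windows each met with probability 0.6, three give 0.6³ = 21.6% and four give 0.6⁴ = 13.0%. The ratio only restates the assumed 0.6. The 13% for one component also lies below the 20% planned for the whole composite, which cannot exceed its component.

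**Conclusion.** Wrong as written. Item 1 sets two incompatible time limits for the postnatal component of the primary outcome, and nothing elsewhere in the protocol reconciles them. This rests only on 42 days being longer than a month and on both limits standing in the current text.

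The consequence is a primary endpoint left open between readings that can give different completion rates. The size of that difference cannot be derived from the protocol. The power figures at rates other than 20% vs 30% are conditional on assumed rates and an ICC of 0.01. With ten clusters per arm, the large-sample approximation is if anything slightly favourable.

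The defect can be repaired without loss if one definition is fixed before outcomes are compared by arm.

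**What to change.** Before any comparison by arm, amend item 1 of Outcome and process indicators so that one time frame governs:

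1. Strike the one-month limit. This is the version consistent with the Introduction, the Summary and the Data collection rounds.
2. State whether one contact in each of the four windows is required, or whether four contacts at any time up to the end of the last window suffice.
3. Give a closing day for the six-week window that the existing round-five visit and facility records can ascertain.
4. Point Objective 1A and the Summary to this definition.

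The cost is a short amendment, with no new data item and no extra fieldwork. It concerns outcome measurement only, not care.

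Moving round five later is optional and not needed for the repair. It would also cost more than it seems. A woman recruited at 20 weeks on 30 September 2024 reaches 40 weeks about 17 February 2025 and six weeks postpartum about 31 March 2025, already past the stated February 2025 end of follow-up.

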**Data collection**

Data will be collected by trained independent data collectors a maximum of five times at households and from health facility records.

First, we will collect data when the mother’s gestation is 20th to 26th week when she formally recruited for subsequent follow-up. This period matches with the time when a mother became pregnant after the start of the intervention process in the intervention cluster. In other words, the mothers who enter the first data collection and follow-up phase on their 20th to 26th week of gestation has been exposed to interventions since they were pregnant. In this first round of data collection, data will be collected on basic socio-demographic and important variables for important covariates such as wealth status indicators, distance to health facility, history of healthcare utilization during the previous pregnancy and delivery.

Follow-up data collection will include the second to the fifth rounds of data collection. The second round will be 10 weeks after the first data collection (30^th^ to 36^th^ week of gestation). This data collection will mainly focus on information about variables related to the continuation of antenatal care utilization and whether the mother had pregnancy related complications and severe sickness, including information on received healthcare for sickness.

The third round of data collection is on the fourth day after delivery. The main variables in this round of data collection include variables on antenatal care completion, delivery information such as place of delivery, delivery attendant, utilization of postnatal care during the WHO recommended first 24 hours and 48-72 hours after birth, whether the mother received any financial, transport, or family care support from the COLs support system to reach to health facility, whether the mother stayed in the maternal waiting shelter nearby health facilities the immediate days before delivery, delivery outcome (livebirth or stillbirth). Additional information will include about maternal and newborn complications during delivery, essential newborn care provided during delivery (resuscitation, umbilical care, thermal care, initiation of breastfeeding, treatment for severely sick and premature babies).

The fourth round of data will be collected two weeks after delivery (10 days after the third data collection) on key first week survival, first week occurrence of morbidity, emergency help received for those who had serious sickness and utilization of postnatal care during the WHO recommended 7-14 days after birth, and essential baby care within the first two week. The final and fifth round of data collection will take place six weeks after delivery. This data collection will include variables on the first month and six week essential postnatal maternal and neonatal care, first month and six-week survival of the newborn, and information on sickness and emergency healthcare received for sickness in this period.

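### The last interview falls at six weeks, just when the fourth postnatal contact is due, and the same definition also limits contacts to the first month, so contacts made shortly afterwards may go uncounted

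*Protocol*

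**What the plan says.** Under Outcome and process indicators, item 1, full completion requires at least four antenatal contacts, a skilled facility delivery, and that the mother "received at least four postnatal care (first 24 hours, 48-72 hours, 7-14 days, and six weeks after delivery"). The sentence then adds that these are to come "from HEWs or other health professionals within the first month after delivery".

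Under Data collection, information is gathered "a maximum of five times at households and from health facility records". The rounds that bear on postnatal care are:

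- Round three: "The third round of data collection is on the fourth day after delivery".
- Round four: "The fourth round of data will be collected two weeks after delivery (10 days after the third data collection").
- Round five: "The final and fifth round of data collection will take place six weeks after delivery". Its content is given as follows: "This data collection will include variables on the first month and six week essential postnatal maternal and neonatal care".

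The Summary sets the end of observation: "Then they will be followed until six weeks postpartum between June 2024 and February 2025". The Protocol gives no visit window for round five, no latest date for the six-week contact and no date for the extraction of facility records.

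**The concern.** Two things do not fit together. First, a contact at six weeks (day 42) cannot also lie within the first month (28 to 31 days); the two limits in one sentence are 11 to 14 days apart. Second, if the six-week contact is the one that counts, it is asked about at the moment it becomes due and nothing is scheduled afterwards.

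Completion is a composite, so one component missed at the end can turn a completer into an apparent non-completer. The Protocol's own background makes contacts near or after this date plausible: the Statement of the problem and the Post-natal care section both describe a custom of staying at home for about 40 days after birth, and the latter also mentions 49. At stake are the level of completion in both arms and the absolute difference between them. A statistical analysis plan could define the scoring rule, but it could not recover contacts that were never observed.

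**Working it through.** **Timing of each contact against the round that captures it**

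| Required contact | Round that asks about it | Is the window closed by then? | Later round as back-up |
|---|---|---|---|
| First 24 hours | Three, day 4 | Yes | Four and five |
| 48-72 hours | Three, day 4 | Yes | Four and five |
| 7-14 days | Four, day 4 + 10 = day 14 | Just closing | Five |
| Six weeks | Five, six weeks | No closing date given | None |

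Only the six-week contact lacks both a closed window and a later round.

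**Which time limit is meant?** The Introduction cites guideline timing that ends with a six-week contact, and round five asks about six-week care. Both point to the six-week contact being intended. The first-month clause points the other way; read literally, it would let no six-week contact count. The text does not settle this.

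**The Protocol's own sample size.** Inputs from Sampling strategy and sample size: 20% vs 30%, z = 1.96 and 0.84, ICC 0.01, m = 150.

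- Before clustering: (1.96 + 0.84)² × (0.2 × 0.8 + 0.3 × 0.7) / 0.1² = 290.08.
- Design effect: 1 + 149 × 0.01 = 2.49.
- Product: 722.3, rounded up to 723 per arm, which is the stated figure.

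The last factor as printed would be 1.5 and would give 435, so the stated number rests on the standard design effect. The timing problem does not enter this figure.

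**Effect of missed contacts.** Let f be the share of true completers whose fourth contact comes after the interview and is not recovered. The Protocol gives no value, so every f below is an assumption. With f equal in both arms, observed completion = true completion × (1 − f).

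Power uses 1000 per arm over 10 clusters, so m = 100, design effect 1 + 99 × 0.01 = 1.99 and effective size 1000 / 1.99 = 502.5 per arm. Power = Φ(difference / SE − 1.96), with SE = √[(p₁(1 − p₁) + p₂(1 − p₂)) / 502.5].

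| f | Control | Intervention | Difference | Ratio | Power |
|---|---|---|---|---|---|
| 0% | 20% | 30% | 10 points | 1.5 | 95.8% |
| 10% | 18% | 27% | 9 points | 1.5 | 93.0% |
| 20% | 16% | 24% | 8 points | 1.5 | 89.0% |
| 30% | 14% | 21% | 7 points | 1.5 | 83.5% |
| 50% | 10% | 15% | 5 points | 1.5 | 67.1% |

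Example, f = 30%: SE = √[(0.1204 + 0.1659) / 502.5] = 0.0239; 0.07 / 0.0239 = 2.93; 2.93 − 1.96 = 0.97; Φ = 0.835. These are normal approximations with no small-sample correction for 20 clusters. Keeping the design effect at m = 150 would give 90.9%, 86.7% and 74.6% at f = 0%, 10% and 30%, but 1000 women in 10 clusters means 100 per cluster.

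**Unequal loss, for illustration only.** Losing 20% in control and 10% in intervention gives 16% vs 27% (11 points). Losing 10% in control and 30% in intervention gives 18% vs 21% (3 points, power about 22%).

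**Calendar.** Recruitment runs to September 2024 at 20 to 26 weeks (Participants). A woman enrolled at 20 weeks on 30 September who delivers at 40 weeks (assumed) does so about 17 February 2025. Six weeks later is about 31 March, already past the stated February end.

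**The case against.** Much of the case on the other side stands.

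- **The definition may moot the point.** If the first-month limit prevails, a six-week interview loses nothing that counts. This is true, and it is why the two limits must be reconciled first.
- **A reader might infer that women seen just after the interview are definitely scored as non-completers.** The Protocol states no scoring rule and gives the interview no exact day. The Summary and Objectives ask only for at least four postnatal contacts, without timings; under a count rule, a woman with four earlier contacts would already qualify. If the outcome means care received by six weeks, leaving out a later visit is correct.
- **A reader might infer that round five is the only source.** Facility records are named as well. Recovery from them is uncertain, because the time of extraction is not given and home visits by health extension workers may not be held there, but it is not excluded.
- **A reader might infer that the treatment effect is biased between arms, or that the trial loses its power.** The documents show neither. Data collectors are independent and have no formal information on allocation, which counts against interview timing differing by arm. Equal loss leaves the ratio at 1.5, and the Protocol does not fix the risk difference as its effect measure. At 1000 per arm, power stays above 80% with 30% lost.

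What remains is the overlap itself. Visit windows can be left to other documents, but this Protocol fixes the last round and the end of follow-up at six weeks, and a plan followed as written can miss a component that its primary outcome lists.

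**Conclusion.** The concern holds in a limited form. The primary outcome carries two incompatible time limits, and if the six-week contact counts, its only scheduled ascertainment falls when it is due, with nothing planned later. Contacts made shortly afterwards may be missed unless facility records recover them. That would lower observed completion in both arms and reduce the absolute difference in proportion: from 10 points to 9 at an assumed 10% loss, or to 7 at 30%.

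The true loss cannot be found from the documents and could be nil. The figures assume equal loss in both arms, the planned 20% vs 30%, ICC 0.01 and 100 women per cluster. Bias between arms is a possibility, not a finding. The point should be fixed because it touches the primary outcome and is cheap to correct beforehand, but it does not by itself undermine the trial.

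**What to change.** 1. Reconcile the first-month and six-week wording in the primary outcome definition, and carry the result into the Summary, Objectives and Data collection.
2. If the six-week contact is kept, give it a closed scoring window. This is an outcome definition only and does not change when care is offered.
3. Hold round five, or a final check of facility and health-post records, after that window closes, and state when records are extracted.
4. Record the date of every postnatal contact and score by that date, not by the day of interview.
5. Use the same interview window in both arms.

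Cost: the last round moves about one to two weeks later, with no extra household visit and no extra women. The February 2025 end has to be extended. The latest recruits already need until about the end of March 2025, and two further weeks would take them to about mid-April.
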